The sensorimotor system plays a central role in regulating postural control and balance. Retrospective data suggest that 30% of adolescents presenting with concussion have vestibulo-ocular deficits in the acute postinjury period.^18^ Adolescent players with acute vestibular dysfunction also have worse prognosis^19^ with a fourfold greater risk of developing postconcussion syndrome.^20^ Clinical assessment of sensorimotor function is based on balance tests such as balance error scoring system (BESS), dynamic tasks like the Y Balance Test, or a 3-metre walk test. However, these traditional tests are scored subjectively, and lack the responsiveness needed to detect small but important deficits in sensorimotor performance. Adding wearable sensor technology to traditional balance tests can improve their accuracy, allowing researchers to quantify subclinical balance deficits. Previous research has shown that sensor-based instrumentation of the Y Balance Test provides a reliable and valid measure of movement control,^21 22^ and is more responsive than the traditional reach distance scoring method.^23^ In a study of adolescent rugby union athletes aged 14–18 years, those with a history of concussion had poorer dynamic balance (high sample entropy (SEn)) during Y Balance Tests compared with non-concussed controls.^24^ There is evidence of Quantified Y Balance Tests predictive validity, and elite male rugby union players presenting with greater irregularity in their Y Balance Test movement control were three times more likely to sustain a concussion than the players with more regular Y Balance Test movement control.^23^

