### Physical assessment

Quantified Y Balance Test is a modification of the Star Excursion Balance Test.^37^ A detailed testing protocol has previously published.^24^ Participants position themselves on a platform with hands firmly on their hips. They are instructed to use their non-stance leg to slide a box forward as far as possible with their foot and return to the starting upright position in three defined directions (anterior, posteromedial and posterolateral). Reach distances are recorded to the nearest 0.5 cm. Individuals complete three practice trials, followed by three recorded trials in a randomised order. A failed attempt is noted when any of the following errors occurred: touching of the foot down on the floor before returning to the starting position; placing the foot on top of the sliding box for balance; and flicking or kicking the sliding box for a better performance or any loss of balance.^38^ If an individual meets any of the failure criteria, the reach attempt will be discarded and repeated. During all tests, an inertial sensor (Shimmer3; Shimmer Sensing) is mounted at the level of the fourth lumbar vertebra and secured with a custom-made elastic belt to closely match the acceleration of the body’s centre of mass during the Y Balance Test excursions. Inertial sensor testing will be captured during testing and analysed offline with MATLAB (2018b; MathWorks). Reach distances and the Y Balance Test will be normalised in relation to the individuals’ leg length, and the mean of three trials completed on each direction will be obtained. Movement control during the Y Balance Test will be quantified using the following variables: normalised reach distance and the SEn of the three axes of the gyroscope signal (x, y and z). SEn of the signal of length N=(x1, x2, x3, …, xn), will be calculated using the following formula:

Sample Entropy = −log (A/B)

Our interpretation of SEn scores is underpinned by key theories in the optimal variability during human motor performance, described by Stergiou and Decker, where a low SEn score indicates more regular and less complex movement control during the Y Balance Test reach excursions, while a higher SEn score indicates a higher degree of movement irregularity/complexity.^39^

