PLR metrics will be measured in response to a brief, step-input, white light stimulus (154-millisecond duration; 180-microwatt power) via a Neuroptics PLR-3000 handheld, infrared, automated, monocular pupillometer (Neuroptics). This device is United States Food and Drug Adminstration (FDA) approved and has been used in similar studies of mTBI in adults.^40^ The pupillometer captures dynamic responses 32 times per second, analysing a continuous, 5-second digital video of the pupillary response to light. The metrics quantified by the device software include the following: maximum pupil diameter (steady-state pupil size before the light stimulus), minimum pupil diameter (pupil size after maximum constriction in response to the light stimulus), percentage pupil constriction, latency (time to maximum constriction in response to the light stimulus), peak and average constriction velocity, peak and average dilation velocity and T75 (time for pupil redilation from minimum diameter to 75% maximum diameter). Peak dilation velocity will be calculated from automated slope-based measures obtained by the pupillometer (Microsoft Excel 2016; Microsoft).

Trained research staff will conduct PLR assessments in an environment with a room illumination of approximately 350 lx (moderate photopic viewing conditions). Athletes will focus on a 3-metre distance target with the non-tested eye for ocular fixation and accommodation during a 5-second measurement period. Monocular measurements are to be repeated at least three times for each eye, alternating 1-minute time intervals to allow rapid visual light adaptation, to obtain two to three artifact-free responses per eye. The combined mean of each pupillometry metric is then calculated for at least two assessments without artefacts, defined as blinks or eye movements occurring within the first 3 s of the response.

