### Statistical analysis

All data will be analysed using the Statistical Package of Social Sciences (SPSS) (V.26; SPSS).

Baseline outcomes (concussion history, Y Balance, PLRM) will be summarised using means and SDs for scale variables and frequencies and percentages for nominal variables. We will use histograms to examine the frequency distributions of scale variables, and where normality is assumed, we will use independent t-tests to compare baseline data (PCSS, Y Balance, PLRM), with players categorised into two groups based on self-reported history of concussion in the last 12 months (no concussion in the last 12 months or concussion within the last 12 months). To avoid bias, researchers will be blinded to group title (ie, history of concussion vs no history of concussion). The threshold for statistical significance will p<0.01 for all tests. We will also present mean differences (95% CIs) between groups for scale outcome data.

SRCs occurring throughout the 2022/23 playing season will be summarised using counts (n, %). Time to SRC event will be plotted using survival curves, with participants censored at the end of the playing season. Serial outcome data (PCSS, Y Balance, PLRM, PFAB-TBI) will be measured at 72 hours, 7 days, 14 days, 23 days, 90 days, 180 days and 365 days postconcussion; we will initially determine the number (%) of participants that had returned to baseline at each time point. We will also examine the growth/response curves for each participant, as well as compare curves between known groups; sex and concussion history. As the shape of the time-response curve is uncertain and may vary across each outcome variable, we will calculate summary measures for each participant based on either the peak value, the time to return to baseline or the area under the curve. Area under the curve will be calculated using the trapezium rule (by adding the areas under the graph between each pair of consecutive observations). The most suitable summary measure will be used in the calculation of a median score (IQRs) for each outcome variable. Between-group comparisons will also be made, comparing curves across two known groups, for example, males/females and history of concussion/no history.

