In an exploratory analysis, we will use logistic regression to examine the association between demographic variables (age, sex, previous injury) and recovery at 23-day follow-up. We will run separate models for each outcome measure (PCSS, Y Balance, PLRM, PFAB-TBI). Our previous research^4^ found that 90% of adolescent rugby players return to sport at 23 days postconcussion; this is also the minimal convalesce for adolescent players postconcussion based on Irish Rugby Football Union and World Rugby guidance, which are built around the latest medical research and expert-based opinion.^46^ Full recovery will be defined as a return to baseline (preseason) values for each respective outcome. Initially, we will conduct a series of univariate analyses to determine whether any predictor variables are associated with recovery. Correlations among predictor variables will be calculated to screen for any strong colinearity (r>0.8). Predictors demonstrating a p value less than 0.10 on univariate testing will be entered into a multiple logistic regression analysis. The strength of the predictive model will be determined using R^2^, p values and ORs, with 95% CIs.

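### Recovery is defined as return to a single preseason value with no tolerance or direction, so on one continuous metric an at-or-better reading labels about half of fully recovered players as not recovered at any visit

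*Protocol article*

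**What the plan says.** Under Statistical analysis, the protocol article sets the rule: "Full recovery will be defined as a return to baseline (preseason) values for each respective outcome". The rule, or the same idea, appears in three places in that section:

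- The first serial analysis, at all seven follow-up visits: "we will initially determine the number (%) of participants that had returned to baseline at each time point".
- The per-player summary measures, which are "based on either the peak value, the time to return to baseline or the area under the curve".
- The outcome of the exploratory logistic models, which study the "association between demographic variables (age, sex, previous injury) and recovery at 23-day follow-up", with a separate model for each of PCSS, Y Balance, pupillary light reflex (PLR) and PFAB-TBI.

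Under Physical assessment, the Y Balance outputs are normalised reach distance and sample entropy (SEn) on three gyroscope axes. The pupillometer yields nine metrics: "The combined mean of each pupillometry metric is then calculated for at least two assessments without artefacts". All are continuous. Under Self-report questionnaires, PCSS runs from 0 to 132 and PFAB-TBI from 0 to 48, both sums of integer item scores.

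No section gives a tolerance, a reliable-change limit, the direction that counts as recovered, or the metric that represents Y Balance or PLR in the recovery label. On reliability, the Introduction says only that "sensor-based instrumentation of the Y Balance Test provides a reliable and valid measure of movement control". No SEM or reliability coefficient is printed.

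**The concern.** Baseline and follow-up are both measured with error. A threshold placed exactly at one noisy baseline reading treats every unfavourable fluctuation, however small, as incomplete recovery.

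The error also differs by type of outcome. Questionnaire scores often tie at or near zero, and a tie counts as recovered. Continuous sensor metrics almost never tie. The rule can therefore produce, with no real deficit, a picture of resolved symptoms alongside persisting abnormality on the instruments. The Discussion hopes to learn whether players under-report symptoms while measured metrics remain elevated, and it lists possible persistence of deficits across systems as a reason for long follow-up. A table of percentages recovered built on this rule could not separate that finding from retest noise.

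**Working it through.** **Inputs from the protocol article (Sample size).** Enrolment 250, loss to follow-up 20%, concussion prevalence 10%, SD of SEn 0.22, standardised difference 0.5. Retest reliability (ICC) is not given, so it is an assumption, shown over a range.

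**The plan's own figure.** 250 × (1 − 0.20) × 0.10 = 20 concussed players. This reproduces.

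**One continuous metric, one visit.** For a fully recovered player, let baseline = T + e0 and follow-up = T + e1, with the same true value T and independent, identically distributed continuous errors. Then e1 − e0 is symmetric about zero, so P(follow-up worse than baseline) = 0.5 for any error SD. A simulation with SD 0.22 gives 0.50 at every assumed ICC from 0.50 to 0.95, and 47-49% if SEn is rounded to 0.01. With 20 recovered players the expected number mislabelled is 20 × 0.5 = 10, and the binomial probability of 6 to 14 is 0.96.

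**Sensitivity to a shift.** A practice or maturation gain of 0.5 SD of the retest difference lowers 50% to 31%. An equal drift in the worse direction raises it to 69%.

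**Integer scales.** Here P(worse) = (1 − P(tie))/2. Gamma-Poisson scores were simulated with assumed means of 0.5 to 15 and shapes of 0.3 to 1.

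| Assumed mean, shape | P(tie) | P(worse) |
|---|---|---|
| 0.5, 0.3 | 0.698 | 0.151 |
| 1, 1 | 0.446 | 0.278 |
| 15, 1 | 0.128 | 0.436 |

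The range is about 15-44%. It is no more than about 28% where half or more of players score 0 at baseline.

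**Several metrics all required to return** (not stated in the protocol). With independent errors, 1 − 0.5³ = 87.5% of recovered players fail on three metrics and 1 − 0.5⁹ = 99.8% on nine. At an assumed correlation of 0.8 the figures are 65% and 76%.

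**Time to first return.** A recovered player has not yet returned after k visits only if baseline is the best of k + 1 exchangeable readings, which has probability 1/(k + 1). That is 50%, 33%, 20% and 12.5% after 1, 2, 4 and 7 visits.

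**Effect on an odds ratio (illustration).** Assume true recovery of 90% and 60%, so OR = (0.9/0.1)/(0.6/0.4) = 6.0. If half of recovered players are mislabelled and every unrecovered player is classified correctly, the observed proportions are 0.45 and 0.30, and OR = (0.45/0.55)/(0.30/0.70) = 1.9. If 10% or 20% of unrecovered players are also labelled recovered, it falls to 1.65 or 1.45.

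**What a limit would do.** The retest difference has SD √2 × SEM. Recovered players labelled not recovered (one-sided):

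| Tolerance | Mislabelled |
|---|---|
| none | 50% |
| 1 × SEM | 24% |
| 1.645 × √2 × SEM | 5% |
| 1.96 × √2 × SEM | 2.5% |

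For SEn, SEM = 0.22 × √(1 − ICC). At assumed ICC 0.7, 0.8 and 0.9 the 1.645 limit is 0.28, 0.23 and 0.16 units. A true deficit of 0.5 SD is 0.5 × 0.22 = 0.11 units. It is called recovered with probability Φ(1.645 − 0.11/(√2 × SEM)), which is 84%, 80% and 70%.

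**The case against.** The strongest objection is that this is a condensed article. How a return to baseline is scored (tolerance, direction, metric) could sit in a full protocol or analysis plan that is not shown, and nothing printed rules out a tolerance. That would answer a complaint about missing detail. Here, however, the article prints a definition of full recovery and names the analyses that use it, and the rule misclassifies when applied as printed.

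Several stronger readings are tempting, and the documents do not support them.

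- A reader might infer that players must hit the *exact* baseline value. The text does not say so, and literal equality would not fail half: with SEn rounded to 0.01 only 2-6% would match, so about 94-98% would fail. The 50% belongs to the at-or-better reading.
- A reader might carry *about half* over to every outcome and analysis. It is too high for PCSS and PFAB-TBI. It is also a single-visit figure, so it does not apply to time to first return, nor to the percentages if those are counted cumulatively.
- A reader might conclude that almost nobody could recover on PLR because nine metrics must all return. No section states such a rule.
- A reader might think the whole recovery analysis depends on the threshold. Individual curves, peak values and areas under the curve do not use it, nor does the baseline comparison. Time to return is one of three candidate summaries, and the logistic models are labelled exploratory. Misclassification unrelated to the predictors pulls odds ratios towards 1; it does not create group differences.

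These points narrow the concern. They leave standing the percentages recovered at each visit, the possible time-to-return summary and the 23-day models.

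**Conclusion.** The concern holds for the binary recovery label. On one continuous metric at one visit, an at-or-better rule calls about 50% of fully recovered players not recovered. This needs no reliability figure. It rests on independent, identically distributed retest errors and no practice, maturation or seasonal shift. For PCSS and PFAB-TBI the share is about 15-44%, which depends on assumed score distributions. It would exceed 50% if several metrics had to return together.

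The percentages recovered per visit would understate recovery, more for the sensor metrics than for symptoms. The exploratory odds ratios would be attenuated: 6.0 to about 1.9 in the illustration, whose 90% and 60% are assumptions. The documents do not support a claim that the study as a whole must find persistent deficits, since its curve, peak and area summaries are free of the threshold.

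**What to change.** Make continuous change from own baseline, with 95% CI at each visit, the main recovery analysis. In recovered players without a systematic shift its expected value is zero, so retest error widens the interval without biasing it.

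Where a recovered/not recovered label is kept, define it before any recovery data are classified:

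- Name one metric per domain (for example one SEn measure and one PLR metric) and state the harmful direction.
- Count a player as recovered if no worse than own baseline by more than 1.645 × √2 × SEM. If SEn is judged in both directions, use a band of ±1.96 × √2 × SEM; a two-sided band at 1.645 would mislabel 10%, not 5%.
- State the source of each SEM. The article identifies no between-session SEM: the Y Balance sensor is described only as reliable and valid, PCSS is supported by internal consistency, and no PLR reliability study is described. Where none is available, report continuous change only, or show the label over a range of assumed SEMs.

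The cost is mostly analysis wording, plus the work of finding or justifying the SEMs. The main downside is that the limit misses small true deficits: one of 0.5 SD is called recovered about 70-84% of the time at assumed reliability 0.9-0.7. The continuous change must therefore be reported with the label. Neither analysis removes a practice or maturation shift, and the report should say so.

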### Sample size

We aim to enrol 250 participants at baseline. This figure allows for a 20% loss to follow-up over the entire study and assumes a 10% concussion prevalence over a single playing season. This will generate recovery data from approximately 20 participants presenting with a new concussion. Recruitment will be stratified to include equal numbers of male and female participants (n=125 males; n=125 females).

A sample of 250 participants would also provide sufficient power for detecting baseline difference in sensorimotor function. Our previous research^24^ had a medium effect standardised mean difference (SMD) 0.5 between adolescents with a history of concussion to those with no history for sensorimotor function with SDs of 0.22 units (SEn). Based on an alpha level of 1%, n=180 participants would provide 90% power for detecting a medium effect difference in SEn between groups at baseline.

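### At alpha 1%, 180 players give about 77% power for SMD 0.5, not the stated 90%, even in two equal groups; 90% needs about 242, and the power of 250 depends on a history split that the protocol does not give

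*Protocol article*

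**What the plan says.** The Sample size section of the protocol article first derives 250 players from the expected number of new concussions. It then adds a claim about the baseline comparison: "A sample of 250 participants would also provide sufficient power for detecting baseline difference in sensorimotor function". The support for that claim is previous research that "had a medium effect standardised mean difference (SMD) 0.5 between adolescents with a history of concussion to those with no history", "with SDs of 0.22 units (SEn"), followed by the power statement: "Based on an alpha level of 1%, n=180 participants would provide 90% power for detecting a medium effect difference in SEn".

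The Statistical analysis section fixes the test and the level: "we will use independent t-tests to compare baseline data (PCSS, Y Balance, PLRM") and "The threshold for statistical significance will p<0.01 for all tests". The two groups are defined by self-report as "no concussion in the last 12 months or concussion within the last 12 months". Recruitment is set at 125 males and 125 females. No recruitment target or expected proportion is given for concussion history. The only concussion rate in the Sample size section is that it "assumes a 10% concussion prevalence over a single playing season", which refers to new events during follow-up.

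**The concern.** Alpha, effect size, sample size and power are all stated, so the figure can be checked directly, and it does not come out. This is the only power figure in the article. It supports the first objective under Aims, which asks whether sensorimotor and oculomotor outcomes are affected by concussion history.

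If 180 were enough, enrolling 250 would leave a margin of 70 players. If about 242 are needed even in equal groups, the margin is 8, and a marked imbalance between the history groups removes it. Imbalance is to be expected when groups are formed by what players report rather than by recruitment. A non-significant result for concussion history could then be read as coming from a study with at least 90% power when the true figure is lower.

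**Working it through.** **Inputs.** SMD 0.5, SD 0.22, n=180, alpha 1% and 90% power come from Sample size; the independent t-test and p<0.01 come from Statistical analysis. The raw difference is 0.5 × 0.22 = 0.11 SEn units. Sidedness is not stated; two-sided is taken as the default and one-sided is also tried. The 20% loss to follow-up does not affect a baseline comparison.

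**Formula.** For groups n1 and n2, df = n1 + n2 − 2 and the noncentrality is δ = d × √(n1·n2/(n1+n2)). Power is the probability that a noncentral t with these parameters falls beyond the critical value.

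**Step 1: the plan's own figure.** For 90 v 90, δ = 0.5 × √45 = 3.354 with df 178.

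| Reading of the statement | Power |
|---|---|
| 180 in total, two-sided 1% (critical t 2.604) | 77.2% |
| 180 in total, one-sided 1% | 84.2% |
| 180 per group, two-sided 1% | 98.4% (needs 360 players; 250 are planned) |
| 180 in total, two-sided 5% | 91.6% (contradicts the stated 1%) |

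No reading at 1% returns 90%. Equal groups are the best case for any fixed total, so 77% is the ceiling for 180 in a two-sided test.

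**Step 2: size needed for 90% power.** The normal formula at two-sided 1% gives 2 × (2.576 + 1.282)² / 0.25 ≈ 119 per group. With the noncentral t, 120 per group gives 89.8% and 121 gives 90.1%, so 121 per group, 242 in total. A one-sided 1% test needs 106 per group, 212 in total. A two-sided 5% test needs 86 per group, 172 in total, which is the requirement closest to 180.

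**Step 3: all 250 players, by share with a recent concussion.** The share is an assumption, because the document does not state it. Test two-sided at 1%, SMD 0.5:

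| Assumed share | Split | δ | Power | SMD detectable with 90% power |
|---|---|---|---|---|
| 10% | 25 v 225 | 2.372 | 41% | 0.82 |
| 20% | 50 v 200 | 3.162 | 71% | 0.61 |
| 30% | 75 v 175 | 3.623 | 85% | 0.54 |
| 40% | 100 v 150 | 3.873 | 90% (89.8%) | 0.50 |
| 50% | 125 v 125 | 3.953 | 91% | 0.49 |

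Power first reaches 90% at 102 v 148, a share of 102/250 = 40.8%, or roughly 41%. The 10% row borrows the plan's rate of new concussions as a proxy for past ones.

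**The case against.** The strongest defence concerns 250, the number actually to be enrolled. In equal groups 250 players give 91% power, so the claim that 250 is sufficient can be true although its supporting calculation is wrong. That stands, and it is why the second part of this point is conditional.

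A reader might infer that the study has only about 41% power, because the plan assumes 10% concussions. The document does not support this as a finding. Its 10% is the assumed rate of new concussions in the coming season, used to project about 20 recovery cases; it is not the share with a past concussion. It is a usable proxy, since both cover about a season or a year, but other values are as defensible. The Introduction cites 3 concussions per team per season. With squads of 15 to 25 (an assumption; no squad size is given) and each event in a different player, that is 3/25 = 12% to 3/15 = 20%, and power at 20% is 71%.

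The Discussion lists stratification by concussion history among the study's strengths. That might suggest balanced history groups, but no quota by history appears, and Statistical analysis only categorises players by their self-report.

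Finally, enrolment was set first by the expected number of new concussions, and mean differences with 95% CIs will be reported, so imprecision would be visible. This limits the harm but does not correct the figure. None of these arguments touches the n=180 error.

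**Conclusion.** The power statement is wrong as written. At the stated 1% level and SMD 0.5, 180 players in equal groups give 77% power two-sided (84% one-sided), and 90% needs about 242. This rests only on the document's own inputs and the two-sided default, and the one-sided reading does not rescue it. That 180 resembles a 5% calculation is an observation about the numbers; the document does not say how the error arose.

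The adequacy of 250 is unsupported rather than shown to be false. It holds in near-equal groups and falls below 90% once fewer than roughly 41% of players report a recent concussion. How far below depends on a share that the document does not give. Confidence is high on the n=180 error and moderate on the practical effect of imbalance.

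**What to change.** In the Sample size section:

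1. Replace the n=180 statement: at two-sided 1% and SMD 0.5, 180 players in equal groups give about 77% power, and about 242 are needed for 90%. State that the test is two-sided.
2. Report the power of 250 over plausible history splits, labelled as assumptions (41%, 71%, 85%, 90% and 91% at 10%, 20%, 30%, 40% and 50%), with detectable SMDs of 0.82, 0.61 and 0.54 at the first three. If 10% is used, say that it is borrowed from the new-concussion rate.
3. Make the claim of sufficient power conditional on roughly 41% or more of players reporting a concussion in the last 12 months, or remove it.

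The cost is wording only. No extra players are needed and the analysis does not change. The downside is a less favourable stated figure.
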